## Method/Design

### Study design

The multicenter randomized clinical MESSI trial is designed to compare MOCA™ and RFA in the treatment of SSV insufficiency. Patients with primary SSV insufficiency, meeting eligibility criteria, will be included at the outpatient clinics of the participating hospitals after giving written informed consent. The procedures are performed or supervised by dedicated vascular surgeons, who have performed over 20 procedures of both treatment modalities.

The following Dutch vascular centers are participating in the MESSI trial: St. Antonius Hospital Nieuwegein, Rijnstate Hospital Arnhem and Rode Kruis Hospital Beverwijk.

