### Recruitment

A total of 160 patients with primary SSV insufficiency will be included in the MESSI trial after signing informed consent (Figure 1). Before treatment begins, a vascular surgeon or dedicated physician assistant will perform a physical examination. The Clinical Etiology Anatomy Pathophysiology (CEAP) score [18] and VCSS [19] are determined. Insufficiency of the SSV is defined by duplex ultrasound as a retrograde flow >0.5 seconds after calf compression while standing [20].

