### Randomization

Patients will be randomized directly after inclusion by the treating vascular surgeon or physician assistant to one of the treatment arms, using a validated web-based randomization tool (Research Manager, NOVA Business Software, Zwolle, The Netherlands). The 1:1 randomization is performed by blocks of ten with stratification for participating centers.

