### Health status measurement

Health status will be measured according to the following:Short Form-36 (SF-36) is a multidimensional measurement of general health. It yields eight domains of functional health and well-being scores.Aberdeen Varicose Vein Questionnaire [22] (AVVQ) is a validated disease-specific health status measurement for chronic venous insufficiency (patient reported outcome).

Both the SF-36 and AVVQ questionnaires are completed pre-procedural and after 4 weeks, 1 year, 2 years and 5 years of follow-up.

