### Statistical analyses

The study results will be evaluated based on intention-to-treat analysis. Data concerning the 1, 2, and 5 years follow-up will be analyzed for both study groups on an intention-to-treat manner by student t-test (normal distribution) or Mann Whitney U-test (skewed distribution). To test for normality, the Kolmogorov-Smirnov test will be used. The Chi-square test will be used for binomial data. All probability values are two-tailed. *P* <0.05 will be considered significant. Obliteration rates will be presented as Kaplan Meier curves, including censoring in case of loss to follow-up.

An interim analysis will be performed after treatment and at 4 weeks follow-up for the first 80 patients to monitor the progression of the study. Final analysis will be performed after follow-up of the last patient included in this study is completed.

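### The fixed tests for the 1, 2 and 5 year outcomes leave out baseline scores and centre as covariates or strata, and let a normality pre-test choose the hypothesis: a loss of efficiency, not of validity

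*Protocol article*

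**What the plan says.** The Statistical analyses section of the protocol article names the methods. Continuous data at 1, 2 and 5 years are compared between arms "by student t-test (normal distribution) or Mann Whitney U-test (skewed distribution". The route to one or the other is a pre-test: "To test for normality, the Kolmogorov-Smirnov test will be used". For the rest, "The Chi-square test will be used for binomial data", and "All probability values are two-tailed". No covariate, stratified test or model appears there or elsewhere in the article.

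The design supplies information that these tests do not take in. Under Randomization, "The 1:1 randomization is performed by blocks of ten with stratification for participating centers"; the Study design section lists three centres. Under Health status measurement, "Both the SF-36 and AVVQ questionnaires are completed pre-procedural and after 4 weeks", and then at 1, 2 and 5 years. Recruitment and Table 1 show that VCSS is scored at screening and at the same follow-up visits.

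**The concern.** A two-sample t-test, a Mann-Whitney test and a plain chi-square test have no place for a covariate or a stratum. Three things follow.

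- **Baseline.** Part of the spread in follow-up VCSS, AVVQ and SF-36 is explained by where each patient started. If raw follow-up scores are compared, that spread stays in the error term and a chance baseline difference between arms passes into the result.
- **Centre.** Stratified allocation balances centres between arms. A test that does not stratify still counts between-centre variation as error, so its standard error is somewhat too large when centres differ.
- **Pre-test.** The t-test addresses a difference in means; Mann-Whitney addresses a shift in rank order. With the normality test deciding, the hypothesis is unknown until the data are seen and can differ between scales and between visits.

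At stake is the precision and clarity of the clinical and quality-of-life comparisons, and to a much smaller degree the primary comparison. Because the article states these tests, this is a comment on a method it fixes, not on detail it leaves to an analysis plan.

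**Working it through.** **The plan's own figure.** The Sample size calculation gives 74 per arm, from 88% success with RFA, 97% with MOCA, a margin of 2 points, one-sided 5% and 80% power. With the variance under the null constrained to the margin (Farrington-Manning):

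- n = [z(0.95)√v0 + z(0.80)√v1]² / (0.97 − 0.88 + 0.02)²
- v1 = 0.88×0.12 + 0.97×0.03 = 0.1347; the constrained rates are 0.929 and 0.909, so v0 = 0.149
- n = [1.645×0.386 + 0.842×0.367]² / 0.0121 = 73.6, that is 74 per arm; 148/0.925 = 160

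The figure reproduces, so 74 per arm is used below.

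**Baseline adjustment of a continuous score.** The correlation ρ between baseline and follow-up is not in the document; 0.3, 0.5 and 0.7 are assumed. Take an effect that the unadjusted two-sided 5% t-test detects with 80% power at 74 per arm: (1.960 + 0.842)×√(2/74) = 0.461 SD. Then:

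- ANCOVA: variance factor 1 − ρ²; power = Φ(2.802/√(1 − ρ²) − 1.960)
- Change score: variance factor 2(1 − ρ); power = Φ(2.802/√(2(1 − ρ)) − 1.960)

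| Assumed ρ | ANCOVA variance factor | Power, unadjusted | Power, change score | Power, ANCOVA |
|---|---|---|---|---|
| 0.3 | 0.91 | 80% | 66% | 84% |
| 0.5 | 0.75 | 80% | 80% | 90% |
| 0.7 | 0.51 | 80% | 95% | 97.5% |

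At ρ = 0.5, 148 patients give the precision of 148/0.75 ≈ 197 under an unadjusted comparison. In simulated normal data, type I error stayed near 5% with and without adjustment.

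**Skewed, tied scores.** The Background reports a VCSS median of 1 (IQR 1 to 2) one year after MOCA, so plain ANCOVA may not suit that scale. Skewed scores rounded to integers were simulated (assumed log-normal, 74 per arm, 3,000 runs):

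| Assumed ρ (before skewing and rounding) | Mann-Whitney | Plain ANCOVA | Rank-based ANCOVA |
|---|---|---|---|
| 0.3 | 62% | 57% | 64% |
| 0.5 | 63% | 64% | 71% |

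Plain ANCOVA loses to Mann-Whitney at the lower correlation; the rank-based adjusted analysis wins at both.

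**Centre.** Let centre explain a share s of the variance of a continuous outcome (assumed; not in the document). After stratified allocation, the true type I error of the unadjusted test is 2[1 − Φ(1.960/√(1 − s))], and power with adjustment is Φ(2.802/√(1 − s) − 1.960).

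| Assumed s | True type I error, unadjusted | Power with adjustment (nominal 80%) |
|---|---|---|
| 1% | 0.049 | 80.4% |
| 2% | 0.048 | 80.8% |
| 5% | 0.044 | 82.0% |
| 10% | 0.039 | 84.0% |

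The true gain is a little less than the last column suggests, because stratified allocation already lifts the unadjusted test slightly: Φ(0.842/√(1 − s)) is 80.2% at s = 2% and 81.3% at s = 10%.

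**Which outcomes each part reaches.** The primary endpoint, occlusion at 1 year, is binary and has no baseline value. Table 1 schedules no pain score before the procedure. For these two, only centre can be adjusted for.

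**The case against.** The strongest reply has four parts.

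1. *Baseline may already be used.* The Definitions section describes clinical success as improvement in VCSS, which is relative to the pre-treatment score. The article does not say whether raw scores, changes or responder status are compared. This stands: it cannot be said that baseline is ignored outright. The table shows, however, that change scores have less power than adjustment at every correlation tried.

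2. *The pre-test does no demonstrated harm.* A reader might infer that Kolmogorov-Smirnov is too weak at this sample size to flag skewed scores, so that the t-test would usually be picked. The document does not support this, because it does not say whether the p-values are corrected for an estimated mean and SD. For clearly skewed continuous data (gamma, shape 2; 58 or 74 observations) simulated rejection rates ran from about one in ten to one in five uncorrected, but from 73% to 83% with the Lilliefors correction. For tied integer scores matching the one-year VCSS quartiles, even the uncorrected test rejected in over 99% of samples, so VCSS would go to Mann-Whitney. Had the t-test been picked for the gamma data, its type I error was 5.0% at 74 and 4.9% at 58 per arm. What remains is that the hypothesis depends on the data.

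3. *The endpoints that drove the sample size gain little.* This stands. Baseline adjustment reaches secondary scores only, and the centre effect with three centres is probably small.

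4. *Covariates are commonly left to an analysis plan.* That would answer a complaint of silence. Here the article states tests that cannot take covariates or strata.

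**Conclusion.** The point holds as one of efficiency. The stated tests are valid, but they are less precise than the data collected would allow for the secondary continuous scores, and they leave the hypothesis for those scores to a pre-test. The gain from baseline adjustment is a variance cut of 9% to 49% over assumed correlations of 0.3 to 0.7. It rests on that assumption and, for skewed scores, on using a rank-based or ordinal model. Leaving out centre makes the tests slightly conservative: type I error of about 0.049 to 0.039 if centre explains 1% to 10% of variance, itself an assumption, calculated for a continuous outcome and not for the binary primary endpoint.

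A reader might go further and infer inflated false-positive rates or an undermined primary analysis. Neither follows: type I error is at or below nominal in every calculation above, and the primary endpoint is touched only through centre. This is an improvement worth making because it costs almost nothing, not a defect that puts the trial's conclusions in doubt.

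**What to change.** Replace the test-selection wording in Statistical analyses with methods fixed in advance:

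- **AVVQ and SF-36:** a model with the baseline score and centre as covariates, rank-based if the scores are expected to be skewed; state which in advance.
- **VCSS:** an ordinal or rank-based model adjusted for baseline and centre, since plain ANCOVA can lose to Mann-Whitney on skewed tied scores at low correlation.
- **VAS pain:** one fixed method adjusted for centre.
- **Binary endpoints, including the primary:** a centre-stratified (Mantel-Haenszel weighted) risk difference with its confidence interval.
- **Normality pre-test:** delete it.

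State also whether clinical success is analysed as a follow-up score, a change or a responder status. The cost is revised wording and a little more programming. Every variable is already collected, and the sample size stays at 160.

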**Discussion:**

The hypothesis of the MESSI trial is that the anatomic success rate of MOCA™ is not inferior to RFA. The second hypothesis is that post-procedural pain is significantly less after MOCA compared to RFA.

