### Study objectives

The aim of the study is to show that MOCA™ has no inferior anatomical success compared to RFA at 1 year follow-up. The secondary aim is to evaluate post-procedural pain, which is hypothesized to be significantly less after MOCA™.

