### Sample size calculation

Power analysis is calculated for anatomical success at 1 year follow-up after endovenous treatment of the SSV. The calculation is based on the hypothesis that MOCA™ will have no inferior occlusion rates at 1 year after treatment compared to RFA. The meta-analysis by Van de Bos *et al*. showed anatomical success rates of 88% after RFA [10]. Our recent study on MOCA™ in SSV showed an occlusion rate of 97% in the group treated according to our current study protocol [17]. A Chi-square test with a one-sided 0.05 significance has a power of 80% to observe no difference between both groups, when each group consists of 74 patients (non-inferiority principle, range 2%). The study population of both groups will consist of 148 patients. Corrected for 7.5% lost to follow-up, the total study population will consist of 160 patients.

Pain is an important secondary outcome parameter. A sample size calculation is also performed for this endpoint based on the hypothesis that MOCA™ will have lower post-procedural pain scores, as measured by a 100-point pain score, during the first two weeks after surgery. To evaluate a 30 percent reduction in post-procedural pain, 58 patients per group are needed (alpha 5%, power 80%). This analysis will be performed after inclusion and randomization of at least 58 patients in each group.

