### Primary endpoints

The primary endpoint is anatomic success after treatment of SSV insufficiency with MOCA™ or RFA at 1 year follow-up. Anatomic success is defined as occlusion of the treated vein and proven with duplex ultrasonography.

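### The trial is sized for non-inferiority with a 2-point margin at one-sided 0.05, but the stated analysis is a two-tailed chi-square test of equality that does not use the margin

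*Protocol article*

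**What the plan says.** All places are in the protocol article.

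- **Hypothesis (Abstract, Discussion):** "The hypothesis of the MESSI trial is that the anatomic success rate of MOCA™ is not inferior to RFA".
- **Study objectives:** "The aim of the study is to show that MOCA™ has no inferior anatomical success compared to RFA at 1 year follow-up".
- **Primary endpoints:** "The primary endpoint is anatomic success after treatment of SSV insufficiency with MOCA™ or RFA at 1 year follow-up". Success is occlusion on duplex, so the endpoint is binary.
- **Sample size calculation:** a chi-square test at one-sided 0.05 with 80% power, "when each group consists of 74 patients (non-inferiority principle, range 2"%). The inputs are a meta-analysis that "showed anatomical success rates of 88% after RFA" and the group's own cohort, which "showed an occlusion rate of 97% in the group treated according to our current study protocol". The power is worded as the chance of seeing no difference between the groups.
- **Statistical analyses:** "The Chi-square test will be used for binomial data. All probability values are two-tailed". P below 0.05 counts as significant. Obliteration rates are also to be shown as Kaplan-Meier curves, with no comparison attached. The section gives no margin, no confidence limit and no rule for concluding non-inferiority.

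**The concern.** The ordinary chi-square test has equality as its null hypothesis. The trial's question is whether MOCA is more than 2 points worse than RFA. The two questions differ most where the test is not significant: in a trial of this size that outcome is compatible both with no loss and with a large loss.

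The sample size section's wording about seeing no difference invites a reader to take non-significance as success. The two sections also disagree on sidedness: the trial is sized at one-sided 0.05, while every P value is to be two-tailed. At stake are the validity of a non-inferiority claim and the power to make one.

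**Working it through.** **Inputs.** RFA 88%, MOCA 97%, margin 2%, one-sided alpha 0.05, power 80% and 74 per group come from Sample size calculation. The two-tailed test at 0.05 comes from Statistical analyses. Assumptions: the 2% is percentage points on the risk difference, the chi-square has no continuity correction, and all 74 per arm are evaluable.

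**1. Reproduce the plan's 74.** Farrington-Manning formula:

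n = (z₁₋α·s₀ + z₁₋β·s₁)² / (p_M − p_R + margin)²

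- s₁ = √(0.97×0.03 + 0.88×0.12) = √0.1347 = 0.367.
- The estimates restricted to a difference of −0.02 are 0.9088 and 0.9288, so s₀ = √(0.9088×0.0912 + 0.9288×0.0712) = 0.386.
- n = (1.645×0.386 + 0.842×0.367)² / 0.11² = 0.891/0.0121 = 73.6, so 74 per group.
- 148/0.925 = 160, as stated.

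Sizing a plain difference test without the margin gives 105 (one-sided) or 134 (two-sided) per group. The margin was therefore a real design input, and it is the analysis section that drops it.

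**2. What each test does at 74 per arm.** Exact enumeration over all 75×75 outcomes: the product of the two binomial probabilities is summed over the outcomes that meet each criterion, with RFA truly 88%. The chi-square is z = (p̂_M − p̂_R)/√(2p̄(1−p̄)/74), non-significant if |z| < 1.96. The score test uses the null difference −0.02 and passes if z > 1.645.

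| True MOCA rate | Chi-square not significant | Chi-square significant for MOCA | Score non-inferiority test passes |
|---|---|---|---|
| 97% (planned) | 41.7% | 58.3% | 84% |
| 86% (at the margin) | 93.5% | 1.0% | 5.3% |
| 83% | 86.1% | 0.2% | 1.6% |
| 78% | 62.8% | below 0.1% | 0.2% |

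**3. Is a significant result informative?** Yes. No outcome that is significant in MOCA's favour fails the margin test, and none that is significant in RFA's favour passes it. Only the non-significant result is silent on the margin. At the planned rates, 84% − 58% = 26% of trials would meet the margin while the chi-square is not significant.

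**4. One illustrative data set.** With RFA 65/74 and MOCA 59/74 the difference is −8.1 points. The pooled rate is 124/148 = 0.838, z = −0.0811/0.0606 = −1.34 and P = 0.18. The Wald 95% interval runs from −19.9 to +3.7 points. The result is not significant, yet it is far from excluding a 2-point loss.

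**5. Cost of the sidedness conflict.** If two-tailed 0.05 is carried to the margin as a 95% interval:

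- n = (1.96×0.386 + 0.842×0.367)² / 0.0121 = 93.8, so 94 per group.
- Power at 74 by the unpooled formula is Φ(0.11×√74/0.367 − 1.96) = Φ(0.62), about 73%.

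**The case against.** The best defence is that the sample size section already ties the 1-year endpoint to non-inferiority, one-sided 0.05 and 2%, and that the later chi-square sentence is a generic line for all binary outcomes. It stands that the margin was built into the design. It does not remove the conflict. The endpoint is binary, so the sentence covers it, the two-tailed rule is stated for every P value, and no exception is made. This is a stated test that does not match the hypothesis, not a detail left to an unseen analysis plan.

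Three stronger readings are tempting, and the documents do not support them.

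- **That the plan will accept a non-significant result as non-inferiority.** No such rule is written. The wording about seeing no difference makes the misreading likely, but the 94%, 86% and 63% apply only if someone makes it.
- **That the stated test cannot support the main claim at all.** A result significant for MOCA does establish non-inferiority (step 3). The accurate complaint is lost power and an uninterpretable non-significant result.
- **That relying on intention-to-treat is part of the error.** The article says "The study results will be evaluated based on intention-to-treat analysis" and does not exclude a supportive analysis. Further analysis sets are commonly left to the full protocol or analysis plan. No crossover rate is given, and crossover does not always favour non-inferiority: if MOCA is truly better, it shrinks that advantage.

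**Conclusion.** The point holds in this form: the stated primary test does not match the stated hypothesis, and its sidedness contradicts the sample size calculation.

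The size depends on the direction. At the rates the trial was planned on, the two-tailed chi-square supports the claim in 58% of trials, against about 84% for the margin test and the 80% intended. Where MOCA is at or beyond the margin, reading non-significance as success would produce a false claim in 63% to 94% of trials over the rates examined, against 0.2% to 5.3% for the score test. The first comparison follows from the test as written, and the second is conditional on an unwritten decision rule.

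Both rest on 74 evaluable patients per arm, RFA at 88% and the 2% taken as percentage points. The figure of 74 is not in error on its own inputs.

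**What to change.** In Statistical analyses, add a sentence for the primary endpoint:

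- The primary analysis is the MOCA minus RFA difference in 1-year anatomical success, with a two-sided 90% score interval (Miettinen-Nurminen / Farrington-Manning). This matches the one-sided 0.05 of the sample size.
- Non-inferiority is concluded only if the lower limit is above −2 points.
- This analysis is exempt from the rule that all P values are two-tailed.
- A non-significant chi-square is not evidence of non-inferiority.

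In Sample size calculation, reword the power as the power to show non-inferiority within the margin. Keep the chi-square for the other binary endpoints. A per-protocol run with the same interval is optional support.

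Cost: wording only, with no new data or patients, provided one-sided 0.05 is kept. If a 95% interval is preferred, the article should restate the power at 74 per group as about 73%, or re-size to 94 per group before allowing for loss to follow-up.

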### Publication of data

Data will be published after all patients had a follow-up period of 1 year, regardless of the outcome of the study. Separate publication of data on pain, initial technical success and short-term follow-up can be published earlier. Long-term results will be published after 2 or 5 years follow-up. Co-authorship will be assigned according to the ‘Recommendations for the Conduct, Reporting, Editing, and Publication of Scholarly Work in Medical Journals’ of the International Committee of Medical Journal Editors [23].

### Definitions

Anatomical success is defined as occlusion of the treated SSV segment, measured with duplex ultrasonography.

Clinical success is defined as the objective improvement of clinical outcome after treatment, measured with the Venous Clinical Severity Score (VCSS).

Initial technical success is defined as the safe placement of the device at the predefined distance from the SPJ, treatment of the SSV without technical problems and occlusion of the treated SSV directly after treatment.

#### Failure of treatment

Failure of treatment is defined as follows:Type 1 (non-occlusion): the treated vein failed to occlude initially and never occluded during the follow-up.Type 2 (recanalisation): the treated vein occluded directly after treatment, but recanalized, partially (>10 cm) or completely, at a later time point during follow-up. Type 2a: recanalization of the entire treated segment of the vein.Type 2b: partial recanalization (open segment >10 cm) [24].

Post-procedural complications (complications occurring within 30 days after treatment) are defined as follow:Major complication: deep venous thrombosis, pulmonary embolism, skin burn, or nerve injury.Minor complication: ecchymosis, superficial phlebitis, hyperpigmentation, induration, wound infection of the puncture site, or prolonged pain >1 week.Sclerosans-related complications.

The duration of procedure includes the time of the procedure, starting from puncture of the vein to the extracting of the catheter, skin-to-skin contact.

